#### Online quantitative surveys (Aims 2–3).

Eligible participants in the quantitative portions of the study will read an informed consent form provided in an online REDCap survey [49]. Eligible participants will indicate with check boxes that they have read each paragraph in the consent form and will be provided with a phone number to call if they have any questions that a non-study team member can answer. After all paragraphs are checked, the eligible participant will be invited to provide a response to confirm their consent or non-consent to participate in the study. Informed consent will be obtained before participants will be allowed to view and to participate in the online REDCap survey for which they are eligible (**Appendix**).

#### Costing surveys (Aim 4).

CCIHP staff (including external facilitators and administrative staff involved in GlobalConsent) and university GlobalConsent implementation team members will complete costing forms regularly, either monthly or weekly, depending on the implementation phase. These individuals will receive a consent form to sign, indicating their agreement to participate. The consent form will include an information sheet, a statement confirming that they have read and understand the information sheet, a statement agreeing to participate in the survey, and contact information for a person who can answer any questions or concerns. The information sheet will cover the purpose of the costing surveys, how the data will be collected, used, and stored, the voluntary nature of participation, an assurance of confidentiality, risks and benefits of participation, and procedures to manage any risks (**Appendix**).

### Additional consent provisions for collection and use of participant data and biological specimens {26b}

There are no additional consent provisions for the collection and use of participant data in this study. No biological specimens are being collected.

## Interventions

### Explanation for the choice of comparators {6b}

A local implementation team at each participating university will deliver the GlobalConsent intervention. This study will vary the implementation strategies that are delivered, with some universities using lower-intensity implementation strategies (LIS) and other universities using higher-intensity implementation strategies (HIS). Implementation strategies in the LIS group model standard approaches to deliver online sexual violence primary prevention programs in universities in the U.S. Implementation strategies in the HIS group were selected from those used in the GlobalConsent efficacy trial [33, 50, 51], from the literature on learning collaboratives [34], and to address barriers and facilitators to program implementation that are common to university settings in Vietnam [35] (Table 2). Nomenclature for specific implementation strategies follows the Expert Recommendations for Implementing Change (ERIC) project [30]. The LIS and HIS implementation strategies are discussed by cluster and organizational level, where key stakeholders were identified to understand the implementation process (Aim 1), drivers and outcomes (Aim 2), and effectiveness (Aim 3).

#### Develop interrelationships between stakeholders and engage university leaders.

Given the demonstrated efficacy of GlobalConsent and the need for high-level institutional commitment for successful implementation, some strategies with university leaders [52] (Deans, Vice Deans, Department heads, Deputy heads) are common to both groups, and the HIS group will receive additional strategies (Table 2). Implementation strategies in both IS groups include prework to obtain formal commitments [30, 34]; passive external web-support with educational materials [34]; *and* pre-implementation educational outreach [34]. Prework, led by CCIHP, involves invitations to each university to take part, a written summary of the proposed project, site-specific dialogue, and written commitments to participate. External web-based support typically is available to US-universities delivering online sexual-violence prevention programs [53, 54]. Our Vietnam-based website will include links to the open-access GlobalConsent study protocol and impact assessments [33, 50, 51]; short videos providing an overview of sexual violence and GlobalConsent in Vietnam and explaining findings in lay terms; one-page briefs with overviews of GlobalConsent and sexual violence among young people in Vietnam; one-page briefs about these findings and sexual violence among young people in Vietnam generally; and answers to frequently asked questions. The two-hour pre-implementation educational outreach led by CCIHP will address misinformation about sexual violence as uncommon, the normative climate for evidence-based prevention, and a description of the GlobalConsent program.

#### Engage potential consumers (university-student users of GlobalConsent).

Internal facilitators in both IS groups will prepare students to become active consumers of GlobalConsent with an email introduction to the program, process and schedule for delivery, procedures for data collection, and consent to take part.

#### Train and support internal implementation facilitators and teams.

Internal implementation facilitators and teams in both IS groups will receive passive external web-support with educational materials and three days of in-person pre-implementation manualized educational outreach on how to deliver GlobalConsent to eligible undergraduate men at their university (Table 3). The three days of in-person training will cover procedures about how to: maintain records on program adoption and penetration among students; identify and invite eligible students to complete an online informed consent, and if completed, a series of short surveys; and send text and email reminders to complete each module within two weeks.

### Intervention description {11a}

Implementation strategies in the HIS group include *additional* strategies (1) to develop inter-relationships between stakeholders and to engage university leadership, and (2) to engage potential consumers (student users) of GlobalConsent (Table 2). CCIHP will provide additional training and support to the implementation team facilitators and members who are delivering GlobalConsent, in service of carrying out the intervention (Table 3).

#### Develop interrelationships between stakeholders and engage university leaders.

Additional implementation strategies to develop interrelationships and to engage university leaders only in the HIS group will include internal-facilitator efforts to inform local opinion leaders [34] about implementation progress via regular emails to university leaders. Additional efforts to inform local opinion leaders will involve meetings with the university faculty (organized and led by university implementation teams) about sexual violence as a problem and prevention with GlobalConsent. Post-implementation educational outreach will entail a one-hour webinar jointly organized by CCIHP and internal implementation teams sharing anonymized findings by IS group and discussing plans to sustain GlobalConsent with future cohorts of university men.

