## Assignment of interventions: Blinding

### Who will be blinded {17a}

Implementation teams at each university will be blinded to the bundle of implementation strategies to which they are being compared. Students will be blinded to the implementation strategies being implemented at their and other universities, except for the strategies to which they are directly exposed. Study team members at Emory University and Georgia State University will be blinded to the assignments of universities until analyses are completed by using a non-ordered numerical assignment to university and study arm in the REDCap database. Members of the data safety and monitoring board will be blinded to implementation strategy assignments until they request to be unblinded.

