### Procedure for unblinding if needed {17b}

Unblinding of implementation strategies assignments may occur before study completion if the Institutional Review Boards, Data Safety and Monitoring Board, or study sponsor deem that unblinding is necessary. Otherwise, unblinding of the study team members will occur upon completion of aims-specific analyses.

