#### Survey-based data collection (Aim 1 checklist; Aims 2–3).

Survey-based data from all target populations will be collected via REDCap [49], a HIPAA-compliant, web-based data system that allows for the secure collection, transfer, storage, and analysis of study data. Customized surveys will be piloted with individuals like the focal populations but at non-study universities to gauge acceptability, inform final revisions, and assess timings to minimize respondent burden (e.g., 10–15 minutes for each leader, faculty, and implementation team survey; 16 minutes for each student survey). The survey implementation protocol described, above, under “Recruitment” will be followed for at each survey wave for faculty, implementation teams, and students to maximize their participation at baseline (~80%) and retention at endline (~90%), based on prior experience surveying students in Vietnam [51].

Measurement time points will vary for each target sample, according to the project timeline (Figure 2). Leaders will be assessed twice, once before and once after implementation. Implementation teams will be assessed quantitatively at four time points: once before the start of any implementation activities, and once immediately before, during, and after implementation of GlobalConsent. Other data on the implementation will come from administrative records collected by the IT company that is responsible for delivering GlobalConsent. Faculty will complete one assessment before implementation (Year 1) and two after the planned 12-week delivery period of GlobalConsent (Years 3, 5). Three surveys will be administered to students at six-month intervals before the planned 12-week delivery period of GlobalConsent, and three six-monthly surveys will be administered at the same interval after implementation, for a total of six assessments. At each occasion, we will send to students’ smartphones an encrypted link to a REDCap survey with ~189 questions measuring two primary behavioral outcomes and seven cognitive/knowledge, attitudinal/belief, affective, and capacity-related secondary outcomes validated in the efficacy trial [33, 50, 51] (Table 6). Secondary outcomes that are included align with our theory of change (Figure 1) and showed evidence of mediation in the trial [50]. A short modification checklist of 5–10 questions will be administered at the end of each GlobalConsent program module to understand participants’ engagement and satisfaction with the module (Table 4).

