**1) Develop Interrelationships Between Stakeholders and Engage University Leaders and Faculty**						
**Obtain formal commitment (prework)**	**+ +**	**+ Site-specific invitation** to participate led by CCIHP; institutional letter of support describing project and collaboration mechanisms; formal contracting	B	2 hr	External (CCIHP)	Universities familiar w/external facilitation No sexual violence prevention/response policy Limited funding for university programs
**Provide passive external web-support and educational materials**	**+ +**	**+ Passive access** to web-based educational materials: links to research articles, short videos, 1-page briefs on sexual violence among young people; the protocol and efficacy of GlobalConsent in Vietnam; answers to FAQs	C	0 hr	External (CCIHP)	Limited time for learning, need for flexibility Standard practice in the United States
**Conduct educational outreach to strengthen formal commitment**	**+ +**	**+ Pre-implementation**: One webinar per group to define sexual violence; rates among young people in Vietnam; acute/chronic effects over life course; primary-prevention EBIs; recap of project description and collaboration; share GlobalConsent website for passive access to educational materials	B	2 hr	External (CCIHP)	Sustain initial commitment Address myth that sexual violence is rare Increase openness to address sexual violence, inequitable gender norms, rape myths Webinar feasible regardless of COVID situation
**Inform local opinion leaders**	**++**	**+ Monthly emails** from trained internal facilitators to university leaders with updates on implementation progress **+ Town halls (3)** with the general faculty to define sexual violence; rates in young people; acute/ chronic effects over life course; primary-prevention EBIs	D D	1 hr 3 hr	Internal Facilitator	Limited time for meetings, need for flexibility in modes of communication, build sustained communication channels between trained internal facilitators and university leaders
**Conduct educational outreach to sustain program**	**+**	**+ Post-implementation**: One webinar to share anonymized findings (by IS group); discuss plans for sustainment (including guidance on how to handle reporting of sexual violence in existing university counseling centers)	A	1 hr	CCIHP and Internal Facilitator	Concern findings will harm univ. reputation Univ. have underutilized counseling centers, staff; no process to address sexual violence

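### The higher-intensity arm's post-implementation webinar shares findings by arm, has no stated date relative to the remaining assessments, and is not reconciled with the blinding of implementation teams

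*Protocol article*

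**What the plan says.** The relevant part of Intervention description {11a} introduces its list as "Additional implementation strategies to develop interrelationships and to engage university leaders only in the HIS group". One item is a one-hour webinar, run by CCIHP together with the internal teams, for "sharing anonymized findings by IS group and discussing plans to sustain GlobalConsent with future cohorts of university men". Table 2 repeats it under outreach to sustain the program: "One webinar to share anonymized findings (by IS group); discuss plans for sustainment". That row carries a single plus sign, the timing code for after implementation and a duration of one hour.

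On blinding, section {17a} states: "Implementation teams at each university will be blinded to the bundle of implementation strategies to which they are being compared". It gives no end point for the teams. It also blinds the Emory and Georgia State study teams until analyses are completed, and {17b} adds that "unblinding of the study team members will occur upon completion of aims-specific analyses". University leaders are not listed among those blinded.

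On follow-up, the survey part of {18a} gives leaders one assessment after implementation, teams a last one after implementation, and faculty two (Years 3 and 5). For students, "three six-monthly surveys will be administered at the same interval after implementation". Dissemination plans {31a} separately promises seminars at participating universities, not limited to one arm, where findings are discussed with university leadership.

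**The concern.** A component given to one arm appears to present results by arm to that arm's leaders and to the teams who run the program there. Those people are also respondents. Leaders complete a second survey and a second key informant interview after implementation, and teams complete a fourth survey and a fourth focus group. Under Outcomes {12} and Table 5 these cover perceived acceptability, appropriateness and feasibility, and attitudes to continuing the program.

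If HIS respondents answer after seeing how the arms compare and LIS respondents do not, part of any Aim 1 or Aim 2 difference could be a reaction to the results rather than to the implementation strategies. The blinding text makes no allowance for such a component.

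**Working it through.** No power or sample-size figure bears on this point, so the check sets the sections side by side and adds some calendar arithmetic.

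**1. Who receives it.** {11a} lists the webinar among HIS-only strategies, and the single plus sign in Table 2 agrees. LIS has no counterpart.

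**2. What it contains.** Both {11a} and Table 2 say findings by implementation-strategy group. The natural reading is results for HIS and LIS.

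**3. Trial component or final dissemination?** It is a listed strategy in Table 2, and {31a} plans separate seminars. It therefore reads as part of the bundle under test. Interim analyses {21b} mentions baseline descriptives, psychometric work and reports to the monitoring board and other oversight bodies; it does not provide for arm-level findings going to sites.

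**4. When it happens.** The text says only that it follows implementation. Participant timeline {13} refers to Figure 2 for HIS dates, and that figure is not available here. The wording elsewhere leans towards the follow-up period: {18b} calls the later student surveys post-implementation surveys, and the Aim 3 model calls that span the post-implementation period.

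**5. How much follow-up remains after delivery.** Six surveys six months apart span (6 − 1) × 6 = 30 months, or 10 quarters, which agrees with the 10 quarters in the Aim 3 model. Assume the first survey is at month 0:
- surveys before delivery: months 0, 6 and 12
- surveys after delivery: months 18, 24 and 30
- 12-week delivery (about 3 months) starting right after month 12: ends near month 15, leaving 30 − 15 = 15 months
- delivery ending just before the first later survey: ends near month 18, leaving 30 − 18 = 12 months

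So about 12 to 15 months of student follow-up remain, with the Year 5 faculty survey also to come. A webinar soon after delivery falls inside follow-up; one held after the last wave and the analyses does not. The text allows both.

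**6. Who is directly exposed.** HIS has three universities:
- leaders: 3 × 5 = 15
- team members: 3 × 5 = 15 using the Sample size {14} figure, or 3 × 8 = 24 using the figure in {31a}

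That is 30 to 39 people if all attend; the upper end equals the 39 per group in the leader and team power calculation. At risk are the second of the leaders' two surveys and interviews and the fourth of the teams' four surveys and focus groups.

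**The case against.** The case on the other side has real force.

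- **Date.** A reader might infer that the webinar takes place while follow-up continues. The text does not say so, and the missing figure may settle it.
- **Blinding.** A reader might infer that blinding is certainly broken. {17a} blinds teams to the content of the other bundle, and anonymised group results need not reveal that content. Leaders are not listed as blinded.
- **Study team.** A reader might infer that the webinar forces early unblinding of the analysts. {17b} concerns study team members only. CCIHP, which co-runs the webinar, performs the randomisation and so knows the allocation by design, and {17a} provides for coded arm labels. Analyst blinding is at risk only if Emory or Georgia State produces arm-labelled results before its analyses end.
- **Meaning of by group.** It may be an aggregation rule that protects universities, since the same Table 2 row records concern about reputation. This is possible, but neither section limits each arm to its own results.
- **Treatment contrast.** Outreach on sustainment is a declared HIS strategy, so its effect on HIS views belongs to the bundle. That holds for the sustainment discussion. It does not make between-arm results from the same trial necessary to that discussion.
- **Late webinar.** A session aimed at future cohorts remains a legitimate component even if it is held too late to move this cohort's outcomes. That is correct, so a late date would not itself be a defect.
- **Reach.** Students and general faculty are not described as attending. The teams' last survey and focus group may come immediately after delivery, before any findings webinar.

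These points limit the finding. They do not supply the missing date or reconcile the webinar with {17a}.

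**Conclusion.** The point holds as an unreconciled design feature, not as a demonstrated breach. One arm is scheduled to receive findings by arm, its implementation teams co-organise the session, and the blinding section neither allows for this nor says when team blinding ends.

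Whether bias follows depends on two assumptions: that the webinar compares the arms, and that it precedes the leaders' or teams' last assessments. If both hold, the self-rated Aim 1 and Aim 2 outcomes of HIS leaders and teams carry a one-sided expectancy effect whose size the document does not allow one to derive.

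A reader might extend this to three of six student waves and two of three faculty waves. The documents support those counts only as upper bounds on an indirect route, through staff who send invitations and reminders. The change is worth making because it is cheap and removes an avoidable ambiguity.

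**What to change.** 1. Keep the webinar and its sustainment discussion in the HIS bundle, but delete findings by group from its content in {11a} and Table 2. Use the published efficacy-trial findings and non-comparative progress data, without showing one university's figures to its peers.
2. State its timing: after the leaders' second survey and interview and the teams' final survey and focus group, by the same rule at all three HIS universities.
3. Present results by arm to both arms at the seminars already planned in {31a}, after the last student survey and the Year 5 faculty survey.
4. Add a sentence to {17a} saying how long team blinding lasts and that the webinar respects it.

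The cost is a change of wording and one webinar agenda, with no effect on sample size or survey schedule. HIS leaders see the comparison later. The leader and team ratings would then describe the bundle up to, but not including, the webinar, and the report should say so.

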#### Engage potential consumers (university-student users of GlobalConsent).

Students only in the HIS group additionally will receive: educational outreach in a pre-implementation in-person orientation to GlobalConsent covering similar topics and three monthly one-hour learning sessions during implementation in which technical questions about program access or progression can be addressed; more intensive intervention to enhance adherence with more frequent email/SMS completion reminders (weekly versus every two weeks for 12 weeks); and demand generation with an option to enter a lottery to win prizes upon program completion.

#### Train and support internal implementation facilitators and teams.

Internal implementation teams and facilitators only in the HIS group additionally will receive leadership training before implementation and external support and technical assistance (TA) during implementation. The two-day leadership training will cover skills needed to champion GlobalConsent with diverse internal stakeholder groups. Topics will cover leadership styles, managing teams, influence without authority, managing conflict, emotional intelligence, negotiation, and leading institutional change. The leadership training also will cover effective ways to facilitate a student orientation to GlobalConsent, facilitate faculty/staff town halls (outreach sessions) about sexual violence, and send effective communications to leaders on implementation progress (Table 3). On-going external support and TA will involve six one-hour quality-improvement team consultations with CCIHP to provide refresher training, discuss implementation progress and modifications, build peer networks, and discuss anonymized data on implementation progress for shared problem-solving. Consultation sessions will be recorded and later coded as part of data collection activities.

